#### **10.7. Provision of Study Results to Investigators, Posting of Information on Publicly Available Clinical Trials Registers and Publication**

Where required by applicable regulatory requirements, an investigator signatory will be identified for the approval of the clinical study report. The investigator will be provided reasonable access to statistical tables, figures, and relevant reports and will have the opportunity to review the complete study results at a GSK site or other mutually-agreeable location.

GSK will also provide the investigator with the full summary of the study results. The investigator is encouraged to share the summary results with the study subjects, as appropriate.

The procedures and timing for public disclosure of the results summary and for development of a manuscript for publication will be in accordance with GSK Policy.

## 12. APPENDICES

### 12.1. Appendix 1 – Abbreviations and Trademarks

#### Abbreviations

|                  |                                           |
|------------------|-------------------------------------------|
| AE               | Adverse Event                             |
| AL-P             | Alkaline Phosphatase                      |
| ALT              | Alanine Aminotransferase                  |
| AST              | Aspartate Aminotransferase                |
| BUN              | Blood Urea Nitrogen                       |
| CO               | Cardiac Output                            |
| CPK              | Creatine Phosphokinase                    |
| CRF              | Case Report Form                          |
| ECG              | Electrocardiogram                         |
| FDA              | Food and Drug Administration              |
| GCP              | Good Clinical Practice                    |
| GSK              | GlaxoSmithKline                           |
| $\gamma$ -GTP    | $\gamma$ -Glutamyltranspeptidase          |
| hCG              | Human Chorionic Gonadotropin              |
| ICF              | Informed Consent Form                     |
| IEC              | Independent Ethics Committee              |
| IRB              | Institutional Review Board                |
| LDH              | Lactate Dehydrogenase                     |
| mPAP             | Mean Pulmonary Artery Pressure            |
| NT-pro-BNP       | N-Terminal pro-B-type Natriuretic Peptide |
| PAH              | Pulmonary Arterial Hypertension           |
| PAP              | Pulmonary Artery Pressure                 |
| PDE              | Phosphodiesterase                         |
| PPH              | Primary Pulmonary Hypertension            |
| PDE-5            | Phosphodiesterase type 5                  |
| PGI 2 | Prostacyclin                              |
| PVR              | Pulmonary Vascular Resistance             |
| RAP              | Right Atrial Pressure                     |
| RHC              | Right Heart Catheterization               |
| SAE              | Serious Adverse Event                     |
| SaO 2 | Arterial Oxygen Saturation                |
| T3               | Triiodothyronine                          |
| T4               | Thyroxine                                 |
| TSH              | Thyroid Stimulating Hormone               |
| WHO              | World Health Organization                 |

**Trademark Information**

| Trademarks of the GlaxoSmithKline
group of companies |
|-----------------------------------------------------------------|
| FLOLAN                                                          |

| Trademarks not owned by the
GlaxoSmithKline group of companies |
|---------------------------------------------------------------------------|
| None                                                                      |

## 12.2. Appendix 2: Liver Safety Required Actions and Follow up Assessments

**Phase III-IV liver chemistry stopping and increased monitoring criteria** have been designed to assure subject safety and evaluate liver event etiology (in alignment with the FDA premarketing clinical liver safety guidance).

<http://www.fda.gov/downloads/Drugs/GuidanceComplianceRegulatoryInformation/Guidances/UCM174090.pdf>

### Phase III-IV liver chemistry increased monitoring criteria with continued therapy

| Liver Chemistry Increased Monitoring Criteria – Liver Event                                                                                                                                |                                                                                                                                                                                                                                                                                                                                                                                                                                                                                                                                                                                                                                                                                                                                                                                                                                                                                                                                                                                                                                                                                                                                                                                                                                                                                                                                                                            |
|--------------------------------------------------------------------------------------------------------------------------------------------------------------------------------------------|----------------------------------------------------------------------------------------------------------------------------------------------------------------------------------------------------------------------------------------------------------------------------------------------------------------------------------------------------------------------------------------------------------------------------------------------------------------------------------------------------------------------------------------------------------------------------------------------------------------------------------------------------------------------------------------------------------------------------------------------------------------------------------------------------------------------------------------------------------------------------------------------------------------------------------------------------------------------------------------------------------------------------------------------------------------------------------------------------------------------------------------------------------------------------------------------------------------------------------------------------------------------------------------------------------------------------------------------------------------------------|
| Criteria                                                                                                                                                                                   | Actions                                                                                                                                                                                                                                                                                                                                                                                                                                                                                                                                                                                                                                                                                                                                                                                                                                                                                                                                                                                                                                                                                                                                                                                                                                                                                                                                                                    |
| ALT $\geq 3 \times \text{ULN}$ with or without bilirubin $\geq 2 \times \text{ULN}$  and with or without symptoms believed to be related to liver injury or hypersensitivity | 
 
• Subject can continue study treatment at the discretion of the investigator (subinvestigator)
 
• Report the event to GSK within 24 hours
 
• Complete the liver event CRF and complete an SAE data collection tool if the event also meets the criteria for an SAE
 
• Perform liver event follow up assessments at discretion of the investigator (subinvestigator) 
 
• Viral hepatitis serology
 
• Only in those with underlying chronic hepatitis B at study entry (identified by positive hepatitis B surface antigen) quantitative hepatitis B DNA and hepatitis delta antibody.
 
• Serum creatine phosphokinase (CPK) and lactate dehydrogenase (LDH).
 
• Fractionate bilirubin, if total bilirubin <math>\geq 2 \times \text{ULN}</math>
 
• Obtain complete blood count with differential to assess eosinophilia
 
• For bilirubin <math>\geq 2 \times \text{ULN}</math>: Anti-nuclear antibody, anti-smooth muscle antibody, Type 1 anti-liver kidney microsomal antibodies, and quantitative total immunoglobulin G (IgG or gamma globulins), serum acetaminophen adduct HPLC assay (quantifies potential acetaminophen contribution to liver injury)
 
 
 
 |

|  |                                                                                                                                                                                                                                                                                                                                                                                                                                                                                                                                                                                                                                                                                                                                                                                                |
|--|------------------------------------------------------------------------------------------------------------------------------------------------------------------------------------------------------------------------------------------------------------------------------------------------------------------------------------------------------------------------------------------------------------------------------------------------------------------------------------------------------------------------------------------------------------------------------------------------------------------------------------------------------------------------------------------------------------------------------------------------------------------------------------------------|
|  | 
in subjects with definite or likely acetaminophen use in the preceding week [James, 2009]) and liver imaging (ultrasound, magnetic resonance, or computerised tomography) and /or liver biopsy to evaluate liver disease: complete Liver Imaging and/or Liver Biopsy CRF forms.
 
 
• Repeat liver chemistries (include ALT, AST, alkaline phosphatase, bilirubin) and perform liver event follow up assessments within 24 hrs if bilirubin <math>\geq 2 \times \text{ULN}</math> and within 72 hrs if bilirubin <math>< 2 \times \text{ULN}</math>
 
• Subject must return at least weekly for repeat liver chemistries (ALT, AST, alkaline phosphatase, bilirubin) until they resolve, stabilise or return to within baseline
 
 |
|--|------------------------------------------------------------------------------------------------------------------------------------------------------------------------------------------------------------------------------------------------------------------------------------------------------------------------------------------------------------------------------------------------------------------------------------------------------------------------------------------------------------------------------------------------------------------------------------------------------------------------------------------------------------------------------------------------------------------------------------------------------------------------------------------------|

1. Serum bilirubin fractionation should be performed if testing is available. If serum bilirubin fractionation testing is unavailable, **record presence of detectable urinary bilirubin on dipstick**, indicating direct bilirubin elevations and suggesting liver injury.
2. All events of ALT  $\geq 3 \times \text{ULN}$  **and** bilirubin  $\geq 2 \times \text{ULN}$  ( $>35\%$  direct bilirubin) or ALT  $\geq 3 \times \text{ULN}$  **and** INR  $> 1.5$ , if INR measured which may indicate severe liver injury (possible 'Hy's Law'), **must be reported as an SAE (excluding studies of hepatic impairment or cirrhosis)**; INR measurement is not required and the threshold value stated will not apply to subjects receiving anticoagulants
3. New or worsening symptoms believed to be related to liver injury (such as fatigue, nausea, vomiting, right upper quadrant pain or tenderness, or jaundice) or believed to be related to hypersensitivity (such as fever, rash or eosinophilia)
4. Includes: Hepatitis A IgM antibody; Hepatitis B surface antigen and Hepatitis B Core Antibody (IgM); Hepatitis C RNA; Cytomegalovirus IgM antibody; Epstein-Barr viral capsid antigen IgM antibody (or if unavailable, obtain heterophile antibody or monospot testing); Hepatitis E IgM antibody
5. If hepatitis delta antibody assay cannot be performed,, it can be replaced with a PCR of hepatitis D RNA virus (where needed) [Le Gal, 2005].

## **12.3. Appendix 3: Definition of and Procedures for Recording, Evaluating, Follow-Up and Reporting of Adverse Events**

### **12.3.1. Definition of Adverse Events**

|                                                                                                                                                                                                                                                                                                                                                                                                                                                                                              |
|----------------------------------------------------------------------------------------------------------------------------------------------------------------------------------------------------------------------------------------------------------------------------------------------------------------------------------------------------------------------------------------------------------------------------------------------------------------------------------------------|
| Adverse Event Definition:                                                                                                                                                                                                                                                                                                                                                                                                                                                             |
| 

• An AE is any untoward medical occurrence in a patient or clinical investigation subject, temporally associated with the use of a medicinal product, whether or not considered related to the medicinal product.

• NOTE: An AE can therefore be any unfavorable and unintended sign (including an abnormal laboratory finding), symptom, or disease (new or exacerbated) temporally associated with the use of a medicinal product.

 |

|                                                                                                                                                                                                                                                                                                                                                                                                                                                                                                                                                                                                                                                                                                                                                                                                                                                                                                                                                                                                                                                                                                                                                                                                                                                                                                                                                                                                                    |
|--------------------------------------------------------------------------------------------------------------------------------------------------------------------------------------------------------------------------------------------------------------------------------------------------------------------------------------------------------------------------------------------------------------------------------------------------------------------------------------------------------------------------------------------------------------------------------------------------------------------------------------------------------------------------------------------------------------------------------------------------------------------------------------------------------------------------------------------------------------------------------------------------------------------------------------------------------------------------------------------------------------------------------------------------------------------------------------------------------------------------------------------------------------------------------------------------------------------------------------------------------------------------------------------------------------------------------------------------------------------------------------------------------------------|
| Events meeting AE definition include:                                                                                                                                                                                                                                                                                                                                                                                                                                                                                                                                                                                                                                                                                                                                                                                                                                                                                                                                                                                                                                                                                                                                                                                                                                                                                                                                                                |
| 

• Any abnormal laboratory test results (hematology, clinical chemistry, or urinalysis) or other safety assessments (e.g., ECGs, radiological scans, vital signs measurements), including those that worsen from baseline, and felt to be clinically significant in the medical and scientific judgement of the investigator (subinvestigator).

• Exacerbation of a chronic or intermittent pre-existing condition including either an increase in frequency and/or intensity of the condition.

• New conditions detected or diagnosed after study treatment administration even though it may have been present prior to the start of the study.

• Signs, symptoms, or the clinical sequelae of a suspected interaction.

• Signs, symptoms, or the clinical sequelae of a suspected overdose of either study treatment or a concomitant medication (overdose per se will not be reported as an AE/SAE unless this is an intentional overdose taken with possible suicidal/self-harming intent. This should be reported regardless of sequelae).

• "Lack of efficacy" or "failure of expected pharmacological action" per se will not be reported as an AE or SAE. However, the signs and symptoms and/or clinical sequelae resulting from lack of efficacy will be reported if they fulfil the definition of an AE or SAE.

 |

**Events NOT meeting definition of an AE include:**

- Any clinically significant abnormal laboratory findings or other abnormal safety assessments which are associated with the underlying disease, unless judged by the investigator (subinvestigator) to be more severe than expected for the subject's condition.
- The disease/disorder being studied or expected progression, signs, or symptoms of the disease/disorder being studied, unless more severe than expected for the subject's condition.
- Medical or surgical procedure (e.g., endoscopy, appendectomy): the condition that leads to the procedure is an AE.
- Situations where an untoward medical occurrence did not occur (social and/or convenience admission to a hospital).
- Anticipated day-to-day fluctuations of pre-existing disease(s) or condition(s) present or detected at the start of the study that do not worsen.

**12.3.2. Definition of Serious Adverse Events**

If an event is not an AE per definition above, then it cannot be an SAE even if serious conditions are met (e.g., hospitalization for signs/symptoms of the disease under study, death due to progression of disease, etc).

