| 
 
To evaluate the safety and tolerability of the new thermostable formulation of FLOLAN (i.e., FLOLAN prepared with the reformulated diluent) when switched from the existing FLOLAN treatment (i.e., FLOLAN prepared with the currently marketed diluent).
 
 | 
 
Incidence and severity of Adverse Events (AEs)
 
Laboratory parameters
 
12-lead ECGs
 
Vital signs
 
Oxygen saturation
 
                                                                                                                                                 |
| Secondary                                                                                                                                                                                                                                                                                            |                                                                                                                                                                                                                                                                                                                                                       |
| 
 
To evaluate the dose adjustment requirements in patients switching from the existing FLOLAN treatment to the thermostable formulation of FLOLAN.
 
                                                                                                          | 
 
The number of events to adjust dose of FLOLAN based on the change from baseline to 3 hours in mean Pulmonary Artery Pressure (mPAP) in a subset of subjects
 
Reason for the change dose of the new thermostable formulation of FLOLAN
 
                                                       |

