| FLOLAN                                             |                                                                                                                                                                                                                                                                                                                                                                                                                                                                                                                                                                                                                                      |                                                                                                                                                                                                                                                                                            |
| Medication errors*                                        | FLOLAN preparation and administration is complex, highly individualized, and continuous, all of which increase the risk of medication errors. Reconstitution of FLOLAN with the current sterile diluent for FLOLAN followed by subsequent prolonged refrigeration or infusion over 24 hours without use of a cold pouch could result in reduced efficacy including possible rebound of PAH symptoms due to decreased room temperature stability of FLOLAN when mixed with the pH 10.5 diluent.                                                                                                                                       | GSK will provide the pH 12 diluent. Patients recruited to this study must be on stable and relatively high doses of FLOLAN. Consequently, patients should have a central line in place, be aware of the routine care required for a central line and aware of the risks of FLOLAN therapy. |

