**12.3.3. Definition of Cardiovascular Events****Cardiovascular Events (CV) Definition:**

Investigators will be required to fill out the specific CV event page of the CRF for the following AEs and SAEs:

- Myocardial infarction/unstable angina
- Congestive heart failure
- Arrhythmias
- Valvulopathy
- Pulmonary hypertension
- Cerebrovascular events/stroke and transient ischemic attack
- Peripheral arterial thromboembolism
- Deep venous thrombosis/pulmonary embolism
- Revascularization

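### PAH worsening that the investigator judges no more severe than expected drops out of the AE and SAE counts, with no threshold set, so the primary safety endpoint can under-count it

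*Supplement*

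**What the plan says.** The latest full protocol text is Amendment 01. The Amendment 02 changes shown do not touch the parts cited here.

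- **Primary endpoint (Section 3).** The first item is "Incidence and severity of Adverse Events (AEs"), alongside laboratory parameters, ECG, vital signs and oxygen saturation. Section 9.4.1 analyses AEs as numbers and percentages of subjects.
- **Exclusion from AEs (Section 12.3.1).** The list of events that are not AEs includes "The disease/disorder being studied or expected progression, signs, or symptoms of the disease/disorder being studied, unless more severe than expected" for that subject. A companion item does the same for abnormal findings linked to the underlying disease, unless the investigator judges them "to be more severe than expected for the subject's condition".
- **Consequence for SAEs (Section 12.3.2).** If an event is not an AE under that definition, "it cannot be an SAE even if serious conditions are met (e.g., hospitalization for signs/symptoms of the disease under study, death due to progression"; both cases in the bracket are given as examples.
- **Inclusion as AEs (Section 12.3.1).** Exacerbation of a chronic or intermittent pre-existing condition, in frequency or intensity, is an AE. Signs, symptoms and sequelae "resulting from lack of efficacy will be reported if they fulfil the definition of an AE or SAE".
- **Cardiovascular page (Section 12.3.3).** "Investigators will be required to fill out the specific CV event page of the CRF for the following AEs and SAEs"; pulmonary hypertension is on that list.
- **Deaths (Section 7.4.1.4).** The Death section of the CRF is completed for every death, SAE or not.
- **Blinding (Section 6.4).** None.

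**The concern.** Leaving the studied disease out of the AE definition is a familiar convention where that disease is measured as the efficacy outcome. Here it meets a different question. Section 4.4 says the study assesses safety after the switch and seeks to support functional comparability of the two diluents. If the switch went badly because a subject received less effective drug, the harm would look like PAH: more symptoms, a longer stay, a readmission.

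Under Appendix 3, whether such an event enters the AE table turns on one unblinded judgement of what was expected, with no criterion and no control arm. An event judged expected also leaves the SAE table and the 24-hour reporting in Section 7.4.1.1, which covers SAEs and related non-serious AEs. Any resulting error runs one way, towards a cleaner picture of the switch.

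**Working it through.** The sample size rests on feasibility (Section 9.2.1) and no alpha, power or margin is given, so the plan has no figure to reproduce. The main check is to set the text side by side.

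**1. Do the rules fix the classification?** Take a stable subject whose breathlessness increases in the second week after the switch.

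- The exacerbation item in 12.3.1 makes this an AE.
- The exclusion item in 12.3.1 takes out "expected progression, signs, or symptoms of the disease/disorder being studied, unless more severe than expected for the subject's condition", so it may not be an AE.
- The lack-of-efficacy item does not decide between them, because it refers back to the AE definition.
- The cardiovascular page in 12.3.3 does not decide either, because it is triggered by events already recorded as AEs or SAEs.

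The text supports both answers, and the investigator chooses.

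**2. Is there a foreseeable event that falls in the gap?** Section 7.2 provides that a subject who cannot be stabilised after the switch stays in hospital longer. Prolonged hospitalisation is a seriousness criterion in 12.3.2. Yet 12.3.2 also gives hospitalisation for the studied disease as an example of what cannot be an SAE once it is not an AE.

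**3. Would other endpoints show it?** From the Time and Events Table (Section 7.1):

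| Measure | Scheduled times after the switch |
|---|---|
| WHO Functional Class | Week 4 or early withdrawal |
| NT-proBNP | 24 hours, Week 4 or early withdrawal |
| Haemodynamics (consenting subset only, target at least 5) | 1, 3 and 24 hours, Week 4, early withdrawal if possible |
| Vital signs, oxygen saturation | 1, 3 and 24 hours, Week 4 or early withdrawal |

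Between 24 hours and Week 4 the scheduled contacts are telephone calls at Days 3 and 7 and Week 2. A PAH admission on, say, Day 10 that resolves by Week 4 and is judged expected could leave no trace in the AE or SAE tables, or in WHO class, NT-proBNP or haemodynamics. A change in dose or concomitant medication during that admission would be recorded, but not as a safety event.

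**4. Size, as illustration only.** Section 4.3 aims for 10 completers. The analysis population is everyone treated, so the denominator may be slightly larger. Exact (Clopper-Pearson) 95% limits with n = 10:

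- 0/10: the upper limit is 1 − 0.025^(1/10) = 0.308, giving 0% to 30.8%.
- 1/10: the lower limit is 1 − 0.975^(1/10) = 0.0025, and the upper limit solves (1 − p)^10 + 10p(1 − p)^9 = 0.025, so p = 0.445. This gives 0.3% to 44.5%.

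Now let p be the true risk that a subject has PAH worsening, and s the share of such events judged worse than expected and so counted. Both are assumptions; the documents give neither. The chance that at least one is counted among 10 subjects is 1 − (1 − p·s)^10:

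| p | s = 1 | s = 0.75 | s = 0.5 | s = 0.25 |
|---|---|---|---|---|
| 5% | 0.401 | 0.318 | 0.224 | 0.118 |
| 10% | 0.651 | 0.541 | 0.401 | 0.224 |
| 20% | 0.893 | 0.803 | 0.651 | 0.401 |

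At p = 10%, for example, counting only half the events cuts the chance of seeing any from 0.651 to 0.401. The loss depends entirely on s.

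**The case against.** A reader might infer that the definitions simply exempt PAH hospitalisation and death from safety reporting. The text does not say that. The sentence in 12.3.2 applies only to events already outside the AE definition, and the exclusion in 12.3.1 is itself conditional on expectedness. Exacerbations are listed as AEs, day-to-day fluctuations are excluded only if they do not worsen, and no death is lost, since all go on the Death form. Listing pulmonary hypertension on the cardiovascular page shows that the protocol foresees PAH events being recorded as AEs.

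A reader might also infer that the protocol itself names PAH rebound as the main harm of the new preparation. It does not. In Section 4.6.1 the words "could result in reduced efficacy including possible rebound of PAH symptoms" stand under medication errors and describe mishandling of solution made with the current pH 10.5 diluent. The table flags medication errors as more likely during the transition, and separately flags local infusion site reactions as more likely with the pH 12 diluent. Ranking the harms would be a reviewer's judgement.

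The strongest practical argument is the population. Sections 5.1 and 5.2 require stable FLOLAN and other PAH therapy for about a month and exclude recent PAH emergencies and anyone not expected to stay stable. In such a subject a PAH admission within four weeks is hard to call expected. PAH status is also tracked by the secondary endpoints, reasons for dose adjustment are listed, and individual listings are planned.

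Much of this stands, and it limits the likely frequency and the severity of the point. It does not supply the missing threshold. The selection argument also cuts the other way: if almost no worsening is expected in these subjects, the exclusion serves little purpose here and only leaves room for inconsistent classification.

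**Conclusion.** The point holds as an avoidable ambiguity in the primary safety endpoint. The counts rest, for PAH events, on an undefined and unblinded judgement of expectedness, and two items in 12.3.1 point in different directions. They can therefore under-count PAH worsening after the switch, and a transient episode between visits could also escape the WHO class, NT-proBNP and haemodynamic endpoints.

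No frequency can be derived from the documents. The 1/10 versus 0/10 comparison assumes that one event occurs and is classed as expected; its intervals overlap widely and the plan intends no formal hypothesis test. It shows only that, with about 10 subjects, a single classification decides whether the SAE table is empty. The conclusion does not rest on any claim that the reformulated diluent delivers less drug. This is a cheap improvement rather than a defect that undermines the study, but it belongs in place before data collection, since events never recorded cannot be reliably recovered later.

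**What to change.** - In 12.3.1, state that from the switch to the follow-up contact any worsening of PAH from the subject's own baseline is recorded as an AE, and as an SAE if a seriousness criterion is met, regardless of whether it was expected.
- Align 12.3.2 with this rule, including its two examples. Deleting the examples alone would change nothing, because the conditional exclusion would remain.
- In the AE outputs under Section 9.4.1, show PAH worsening, PAH hospitalisation and death as separate lines, so that the tables can be read with and without them.

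The change concerns recording and tabulation only; no dosing or management rule is affected. It costs some wording in Appendix 3, a few table rows and a few more AE or SAE reports, some of which will reflect the natural course of the disease. The separate lines let a reader allow for that.
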